### Statistical analysis

The primary analysis will be intention-to-treat. The primary analysis for the quantitative data will involve a mixed-effects multilevel logistic regression model to account for clustering by peer educator group and study site (participants nested in peer educators nested in study sites). These models will include an indicator term for study arm (fixed distribution, direct distribution or control). Outcomes, including past month HIV testing and correct knowledge of status at 4 months, will be modelled as dichotomous variables.

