### Study design

This is a unmasked cluster randomised trial. Individuals are enrolled as members of a peer educator group, with a target enrolment of six FSWs per peer educator (with five allowed if there are recruitment difficulties). The peer educator–FSW group is randomised in a 1:1:1 fashion to one of the three study arms: (1) peer educator distribution of HIVST directly to participants (direct distribution), (2) peer educator distribution of a coupon valid for an HIVST at a fixed distribution point (fixed distribution) or (3) standard of care. Participants will be followed for 4 months from enrolment, with follow-up assessments at months 1 and 4 (figure 1).

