### Setting

This study is taking place in three border and transit towns in Zambia: Chirundu, Livingstone and Kapiri (figure 2). Chirundu and Livingstone are located on the Zambia–Zimbabwe border, and are major transportation points for people and goods. Kapiri is north of the capital, Lusaka, and is a transit hub, with a large weigh station where many truckers stop for the night or longer. Study headquarters and coordination for the three sites is located in the capital, Lusaka.

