### Randomisation

Peer educator groups (the 5–6 women recruited by a particular peer educator and enrolled in the study) are randomised as a unit. Group randomisation occurs after all members of the group have been enrolled in the study and completed their baseline questionnaire. Groups are randomised to one of the three study arms using a computer-generated randomisation list in random blocks of 3, 6 and 9 and stratified by study site (Livingstone, Chirundu and Kapiri). Randomised study arm assignments are placed in an opaque envelope, and once all participants in a peer educator group have been enrolled, the research assistant obtains the envelope from the research coordinator or the site coordinator and opens the envelope with the peer educator.

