### Data collection

#### Baseline survey: enrolment

At the enrolment visit, all participants complete a quantitative questionnaire administered by a research assistant. Quantitative data are collected directly on a tablet. All assessments are conducted in a private room at a time and location that is convenient to the participant. The baseline survey covers broad topics including demographics and household composition, sex work and professional history, reproductive health and contraception, sexual behaviours, HIV testing history, attitudes towards HIVST, access to healthcare, and measures of substance use,^21^ depression,^22^ social support, self-efficacy,^23^ and empowerment.^24^

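### The primary model treats study site, a three-level randomisation stratum, as a random nesting level; two fixed site terms would suit the design better, at no cost and with little effect on the arm comparison

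*Protocol article*

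**What the plan says.** The Statistical analysis section says the primary mixed-effects logistic model is to "account for clustering by peer educator group and study site (participants nested in peer educators nested in study sites". On explanatory terms it says: "These models will include an indicator term for study arm (fixed distribution, direct distribution or control". No other term is named.

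The rest of the design is described as follows:

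- **Setting:** "This study is taking place in three border and transit towns in Zambia: Chirundu, Livingstone and Kapiri".
- **Randomisation, unit:** "Peer educator groups (the 5–6 women recruited by a particular peer educator and enrolled in the study) are randomised as a unit".
- **Randomisation, method:** the list is generated "in random blocks of 3, 6 and 9 and stratified by study site (Livingstone, Chirundu and Kapiri".
- **Study design, ratio:** "The peer educator–FSW group is randomised in a 1:1:1 fashion to one of the three study arms".
- **Baseline survey:** the topics covered at enrolment, before randomisation, include "HIV testing history".

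The article never writes out a random intercept for site. That is the natural reading of site as the top nesting level in a mixed model with arm as the only named explanatory term.

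**The concern.** The two levels of clustering in the model play different roles in the design. Peer educator groups are the randomised units, and about 150 of them are planned, so a random intercept for group is needed and can be estimated. The towns are three named places used as strata and are not randomised. Arms are compared within each town.

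Treating site as random asks the data for a between-town variance from three units. Such an estimate is very imprecise and is often exactly zero. The fitted model then contains arm and group only, and the factor used to stratify randomisation has left the analysis. The software may also report a singular or boundary fit in the primary model of an unmasked trial. The analyst might then have to decide, with the data in view, whether to keep, drop or recode site. A fixed site term avoids that situation.

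**Working it through.** **1. The plan's own power.** Inputs from Sample size considerations: control rate 50%, risk ratio 1.30 (so 65%), 300 women and 50 groups per arm, 20% loss, intracluster correlation 0.03, alpha 0.05 (taken as two-sided).

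- Analysed per arm: 300 × 0.8 = 240. Per group: 240/50 = 4.8.
- Design effect: 1 + (4.8 − 1) × 0.03 = 1.114. Effective n: 240/1.114 = 215.4 per arm.
- SE = √[(0.50×0.50 + 0.65×0.35)/215.4] = 0.0471. Power = Φ(0.15/0.0471 − 1.96) = 89.0% (88.6% with pooled variance). Stated: 89%.
- Status knowledge, 70% against 84%, by the same method: 93.8% (93.5% pooled). Stated: 94%.

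The stated power is reproduced with clustering by peer educator alone. It contains no site component.

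**2. Information in three towns.** Under normality, and even if each town's level were known without error, the 95% interval for an SD runs from √(df/χ²₀.₉₇₅) to √(df/χ²₀.₀₂₅) times the estimate.

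- 3 towns, 2 df: √(2/7.378) = 0.52 to √(2/0.0506) = 6.3.
- 150 groups, 149 df: 0.90 to 1.13.

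**3. How often the site variance is estimated as zero.** The article gives no between-site SD (τ, logit scale) and no enrolment split by town. Assumed here: equal towns, so 900 × 0.8/3 = 240 analysed per town, and an average testing rate of (0.50 + 0.65 + 0.65)/3 = 0.60, so p(1 − p) = 0.24.

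- Sampling variance of a town's logit: v = 1.114/(240 × 0.24) = 0.0193.
- The maximum-likelihood variance is max(0, S/3 − v), where S is the sum of squared deviations of the three town logits and S/(τ² + v) follows χ² on 2 df. Hence P(zero) = 1 − exp[−1.5 v/(τ² + v)].
- τ = 0.2: v/(τ² + v) = 0.0193/0.0593 = 0.326, so P = 1 − exp(−0.489) = 39%.
- τ = 0.5: 0.0193/0.2693 = 0.072, so P = 1 − exp(−0.108) = 10%.
- τ = 0: P = 1 − exp(−1.5) = 78%.

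A simulation of the full logistic mixed model gave 38–41%, 10–11% and 79–82% respectively.

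**4. Effect on the arm comparison.** The same simulation used 150 groups (50 per town), six women per group with 80% retained, and a latent-scale intracluster correlation of 0.03. There were 300 trials per scenario. One HIVST arm was tested against control, with site random, fixed or left out in fits to the same data.

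| Assumed site SD | Type I error: random / fixed / left out | Power at risk ratio 1.30: random / fixed / left out |
|---|---|---|
| 0 | 3.3 / 4.0 / 3.3% | 88.0 / 88.0 / 88.0% |
| 0.2 | 4.3 / 4.0 / 4.3% | 89.7 / 90.0 / 88.7% |
| 0.5 | 4.7 / 5.0 / 3.7% | 87.3 / 87.7 / 84.0% |

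Between random and fixed site:

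- the mean standard error of the arm log odds ratio differed by about 0.001;
- the arm estimate differed by a median of 0.002–0.003 and at most 0.018;
- the significance decision differed in at most 0.7% of trials.

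The Monte Carlo standard error is √(0.05×0.95/300) = 1.3 points for type I error and √(0.88×0.12/300) = 1.9 points for power, so small differences in the table should not be read as real.

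**The case against.** The strongest reply is that the site variance is a nuisance parameter that the article does not plan to report, and that nothing of interest depends on it. Allocation is 1:1:1 within town, so site is nearly balanced across arms. A zero estimate arises mostly when the towns look alike, which is when losing the term costs least. The simulation supports this. Leaving site out altogether at an SD of 0.5 lowers power to 84.0%, yet the random-site model stays at 87.3%, because at that SD it rarely drops the term. This part of the objection stands, and it sets the size of the point.

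It is also fair to say that one sentence in a condensed article may summarise a model set out in full elsewhere. But the sentence does place site among the nested levels of the primary model, so it can be assessed as written.

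Three stronger readings are tempting, and the documents support none of them:

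- **Invalid inference.** A reader might infer that the standard errors do not match the design, or that 2 degrees of freedom for site carry over to the arm test. Arm varies within town, and the stated model has no site-by-arm variation. The simulated error rates lie near 5% or a little below.
- **Wrong sample size.** Stated N and power are reproduced without a site term and do not change under the fix.
- **Omitting baseline testing history is an error.** It is not a stratification factor, and covariate choice is commonly left to an analysis plan, which is not shown. Eligibility also narrows its range, because self-reported HIV-negative women tested within the past 3 months are excluded. In a logistic model, adjustment also moves the conditional odds ratio and can raise its standard error, so a linear-model variance reduction does not carry over.

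**Conclusion.** The point holds as a minor matter of specification. Three purposively named towns that serve as randomisation strata should not be a random level. Their variance cannot be usefully estimated, and a zero estimate is a realistic outcome in the primary model: about 40% of trials at a site SD of 0.2 and about 10% at 0.5. When it happens, the stratifier drops out.

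The effect on the treatment comparison is small. Power differs by at most 0.4 points between random and fixed site, and type I error by no more than the simulation can resolve. There is no evidence of bias or of invalid standard errors.

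The conclusion rests on reading the nesting statement as a random intercept for site, on assumed between-site SDs, and on equal numbers per town. The 2-degree-of-freedom argument needs only the count of three sites.

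**What to change.** State in the Statistical analysis section that the primary model has arm and study site as fixed effects (two indicator terms for the three towns) and one random intercept, for peer educator group. This takes one sentence and 2 degrees of freedom against 150 groups. It leaves sample size and power as they are and brings the model into line with the stratified randomisation and with the clustering used in the power calculation.

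Optionally, prespecify baseline time since last HIV test, with a 'never tested' category, as a fixed covariate. The enrolment survey already covers HIV testing history, so no new survey topic is needed. The cost is 1–3 further degrees of freedom and an odds ratio that is conditional on that covariate. No power figure should be attached to it.

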### Qualitative data analysis

Qualitative data will be analysed using an iterative descriptive approach to characterise and describe the data at their natural level. After all interviews are transcribed and translated, a codebook will be finalised and transcripts will be coded in Dedoose, a cloud-based platform for mixed-methods research.

### Sample size considerations

The sample size calculation was based on the primary end point, testing for HIV in the past month assessed at the 1-month visit, and the secondary end point, proportion of participants who correctly know their status at the 4-month visit. Power calculations were performed using methods for cluster randomised trials, with clustering by peer educator identity. We assume that 50% of participants will have tested in the past month in the control arm based on previous estimates of HIV testing behaviour among FSWs in Livingstone and Chirundu.^29^
^30^ We estimate that in the control group, ∼70% of participants will correctly identify their HIV status, assuming that the majority of those whose status is unknown will report that they are negative, but that approximately half of these individuals will actually be positive. Assuming a 20% loss to follow-up and with 50 peer educators (clusters) per arm, a sample size of 300 participants per arm (900 total) will yield 89% power to detect a risk ratio of 1.30 for recent testing and 94% power to detect a risk ratio of 1.20 for correct status knowledge, assuming a type I error probability of 0.05 and an intracluster correlation of 0.03.

### Confidentiality

To protect participants' confidentiality, no identifying information will be collected during any quantitative or qualitative assessment and all collected data are de-identified. A unique study identification number will be used to link data from an individual participant. Participant identity codes are kept completely separately from electronic data, in a locked cabinet in study offices. The code will be destroyed on completion of the study.

### Data management

Quantitative data are collected directly on a study tablet via CommCare (Dimagi, Cambridge, Massachusetts, USA), a Health Insurance Portability and Accountability Act (HIPAA)-compliant, cloud-based platform for electronic data collection. Qualitative data are collected via an audio recorder, which are transcribed and translated verbatim. Qualitative audio recordings are destroyed on completion of transcription and translation.

### Dissemination plan

The results of this study will be disseminated to community, policy and scientific stakeholders. A results community meeting will be planned on completion of the study at each study site, during which the results of the study will be announced. We will also hold a meeting with the Ministry of Health in Lusaka to disseminate our findings, and submit a report detailing the findings of the study to inform policy. Finally, results will be shared with the scientific community via presentation at international conferences and journal publication.

## Discussion

Despite the high risk and large burden of HIV among FSWs, HIV testing and HIV status knowledge in this population remain far from universal. A number of complex barriers at multiple levels can limit access to HIV testing for FSWs, including fear of stigma and abuse, fear of loss of livelihood, and the financial and time costs of using traditional HIV testing services. HIVST is a promising alternative HIV testing option for FSWs, because it allows for a high degree of privacy, efficiency and flexibility in HIV testing. The overarching goal of the ZEST trial is to provide robust evidence for the development of policy for implementation and scale-up of HIVST in Zambia with a specific focus on ensuring that this technology is accessible to FSWs. Working in concert with the Ministry of Health in Zambia and the WHO, this trial was specifically designed to fill a crucial gap in the evidence by answering two questions: (1) Is HIVST an acceptable alternative to standard HIV testing for FSWs? and (2) Will FSWs access HIVST?

Question 1 is addressed through the direct distribution arm. In this arm, we will be able to assess whether individuals directly given a test actually use the test. By directly giving individuals the test, we are assessing best-case scenario uptake, where there are as few barriers as possible for individuals to access the test kit. The uptake results from this arm of the study will give robust evidence on whether HIVST is an acceptable alternative to standard and currently available HIV testing services. Coupled with qualitative data, we will be able to measure both the uptake of HIVST and participant attitudes towards HIVST. This will lead to an in-depth understanding of why participants did or did not use the test, and how participants view the role of HIVST for HIV testing in the future.

Although uptake and acceptability of HIVST is an important piece of evidence for HIVST policy, the design of this study allows for measurement of a more realistic scenario, in which participants must go to a physical distribution point to collect their kit. Question 2 is thus addressed through the fixed distribution arm. This arm will measure the degree to which barriers to acquiring the HIVST kit in the store affect acquisition and use of the test. This will be tested by implementing the project within existing drug stores and health posts, without changing the hours or geographical locations of existing services. The direct and fixed distribution arms will therefore give two complementary pieces of information—first, are participants using the test kits? and second, are they able to access them independently?

A major strength of this study is that it does not rely on clinic-based sampling or recruitment. A potential benefit of HIVST over existing HIV testing services is that it may allow individuals who are not currently engaged in care or who have never sought HIV testing because of barriers to accessing care to test for HIV. HIVST may therefore be a gateway to care for individuals who have previously been difficult to engage in care. By working through peer educators, rather than in clinics, we will access a different subset of the population. Peer educator programmes have been used in a variety of settings with different sex worker populations to increase HIV prevention knowledge.^31–36^ In many cases, peer educators have unique access to and rapport with FSWs. This study, therefore, is expected to enrol a diverse population of FSWs that is most likely more generalisable than a clinic-based sample, while simultaneously allowing access to populations that may not currently access care.

A major concern with HIVST is the potential for intimate partner violence, for example, if sexual partners find out about HIV status through the test. All participants will be screened for intimate partner violence at baseline, 1 and 4 months. Intimate partner violence is very common in the FSW community, and those who have experienced intimate partner violence will be eligible to participate, although the risks of participating are explained fully. Furthermore, during follow-up peer education visits, peer educators will screen for intimate partner violence, and they will also be available between visits should any issues come up. Finally, a 24-hour telephone line will be available to all participants for any issues, including intimate partner violence, and referral will be made to counselling if desired. All reports of intimate partner violence will be reviewed to determine if they are related to HIVST or trial participation. In this study, we do not offer HIVST for FSWs to test with their clients or other sexual partners. While it is possible that partner testing could be a benefit for some participants, it could also put some at increased risk of violence. We will collect detailed quantitative and qualitative data about individuals with whom participants used the test, if anyone. The results of this study are expected to yield evidence of the impact of HIVST on safety end points, in particular intimate partner violence.

Another safety concern with HIVST is the potential for depression, anxiety or suicidality as a result of learning one's HIV status. Structured interviews will contain screening questions for depression, and peer educators will perform a brief screening on depression, anxiety and self-harm at each visit. Finally, participants will be instructed to call the hotline should they need to discuss their HIV result with anyone or receive counselling.

In conclusion, the results of this study are expected to inform policy aimed at implementation and scale-up of HIVST for FSWs in Zambia. This study will begin to address critical gaps in the literature describing evidence of HIV testing interventions for FSWs in Southern Africa. We expect the results of this trial to have a policy impact resulting in increased availability of HIVST in Zambia.
